## Abstract

**Background:**

The Hospital Elder Life Program (HELP) has been shown to be highly efficient and (cost-)effective in reducing delirium incidence in the USA. HELP provides multicomponent protocols targeted at specific risk factors for delirium and introduces a different view on care organization, with trained volunteers playing a pivotal role. The primary aim of this study is the quantification of the (cost-)effectiveness of HELP in the Dutch health care system. The second aim is to investigate the experiences of patients, families, professionals and trained volunteers participating in HELP.

**Methods/Design:**

A multiple baseline approach (also known as a stepped-wedge design) will be used to evaluate the (cost-) effectiveness of HELP in a cluster randomized controlled study. All patients aged 70 years and older who are at risk for delirium and are admitted to cardiology, internal medicine, geriatrics, orthopedics and surgery at two participating community hospitals will be included. These eight units are implementing the intervention in a successive order that will be determined at random. The incidence of delirium, the primary outcome, will be measured with the Confusion Assessment Method (CAM). Secondary outcomes include the duration and severity of delirium, quality of life, length of stay and the use of care services up to three months after hospital discharge. The experiences of patients, families, professionals and volunteers will be investigated using a qualitative design based on the grounded theory approach. Professionals and volunteers will be invited to participate in focus group interviews. Additionally, a random sample of ten patients and their families from each hospital unit will be interviewed at home after discharge.

**Discussion:**

We hypothesize that HELP will reduce delirium incidence during hospital admission and decrease the duration and severity of delirium and length of hospital stays among these older patients, which will lead to reduced health care costs. The results of this study may fundamentally change our views on care organization for older patients at risk for delirium. The stepped-wedge design was chosen for ethical, practical and statistical reasons. The study results will be generalizable to the Dutch hospital care system, and the proven cost-effectiveness of HELP will encourage the spread and implementation of this program.

**Trial Registration:**

Netherlands Trial register: NTR3842

## Background

In the next 30 years, the proportion of people 65 years and older is expected to increase to account for 25% of the general Dutch population, compared to 15% in 2008 [1]. Older people are at a higher risk for hospitalization. Of every 10,000 people 65 years and older, 3,131 older people were admitted to the hospital in 1995 and 5,521 in 2010 [2]. In 2005, 25 % of the admitted patients in hospitals were 70 years old or older, for totaling 400,000 people [3]. The risk for delirium is significantly associated with age, and in 2005, the Dutch Health Care Inspectorate (IGZ) indicated that 40,000 to 160,000 hospitalized patients 70 years and older suffer from delirium annually in the Netherlands [3].

Delirium is characterized by an acute disruption of attention and cognition [4] and is the main cause of confusion in the general hospital [5]. The DMS-IV criteria for delirium are as follows: a disturbance of consciousness with a reduced ability to focus, sustain, or shift attention; a change in cognition (memory, language, or orientation) or the development of a perceptual disturbance not related to dementia; a quick onset that fluctuates during the day; and an underlying physiological problem or medication as the cause [4].

Patients with delirium are at an increased risk for complications and mortality during a hospital stay. Delirium can further result in adverse events after hospitalization, including lasting functional limitations, persistent cognitive decline, loss of quality of life for the patient and family, re-hospitalization and nursing home admission [6-8]. Unfortunately, nurses and physicians often do not recognize the presence of delirium [5]. Once delirium is diagnosed, standard delirium treatment consists of diagnosis and treatment of the underlying medical condition. Furthermore, management of delirium consists of environmental interventions addressing orientation, day structure, safety and, if necessary, the prescription of (antipsychotic) drugs [5].

Preventing delirium is preferred over treating delirium, and attention should therefore focus on (multi-faceted) prevention interventions. Recently, a meta-analysis of five studies of 1,491 older patients concluded that the perioperative use of antipsychotics may reduce the overall risk of postoperative delirium among older people [9], but the results to date have been inconsistent [10] and some reveal only decreased delirium duration or severity, with either no impact or adverse impact on clinical outcomes [11].

Relatively little high quality research on delirium prevention (not including postoperative treatment) has been published [12], and an approach targeting several risk factors for delirium appears to be the best strategy to prevent delirium [13,14]. Currently, there is increasing evidence that delirium can be prevented through non-pharmacological interventions [10,14,15].

### Aims

In this project, the primary aim is to investigate the (cost-)effectiveness of the Hospital Elder Life Program (HELP) in the Dutch hospital care system; this program has been shown to be effective in the USA for the prevention of delirium in older adults during hospital admission to both internal medicine and surgery departments. HELP has been shown to be effective in reducing the incidence, duration and severity of delirium [15] and decreasing health care costs [16-19]. A second aim is to investigate the experiences of patients, families and volunteers involved in HELP because in the USA, HELP also enhanced patient and family satisfaction with hospital care and improved the quality of care [16]. The introduction of HELP requires a fundamentally different view on the care organization and a change in the care process, including the introduction of methods for early recognition of delirium symptoms combined with care plans, the introduction of an Elderly Care Nurse Practitioner position and the introduction of trained volunteers to provide additional care and psychosocial support.

Although HELP has been disseminated at a number of USA and internationally [20,21], only recently has the first implementation of an adapted HELP program in a European hospital (Spain) been described [22]. The Dutch hospital care system and the patient population are different from the system and patients in the USA. Therefore, it is not possible to extrapolate earlier findings on the effects of HELP to the Dutch system. The HELP materials and protocols will be translated and adapted where necessary in close collaboration with the developer of the HELP program, [name].

## Methods/Design

### Design

A multiple baseline approach (also known as a stepped-wedge design) [23] will be used to evaluate the efficacy and (cost-) effectiveness of the introduction of HELP within the Dutch health care system (Additional file 1: Table S1).

Over a period of 18 months, eight hospital units of the Hospital Gelderse Vallei in Ede and the Diakonessenhuis in Utrecht and Zeist in the Netherlands will successively receive the intervention; new units will start every three months.

To investigate the experiences of patients, families, professionals and trained volunteers involved with the HELP program, a qualitative design study based on the grounded theory approach [24,25] will be conducted.

### Study population

Eligible participants are patients ages 70 years and older who are at risk for delirium and are admitted to the cardiology, internal medicine, geriatrics, orthopedics and surgery units of the two hospitals. The Diakonessenhuis is situated in two locations (one in a university city and one in a smaller town nearby), while the Hospital Gelderse Vallei is located in a more rural area.

Eligible patients will be approached by the nurse on call for participation within 24-hours after hospital admission. Inclusion criteria are being 70 years and older, the absence of delirium at hospital admission and being considered at risk for delirium.

To assess whether a patient is at risk for delirium, we use the three questions of the Hospital Safety Program launched in the Netherlands in 2009 that are part of obligatory hospital care. A review of literature was done before choosing these questions [26]. The nurse will assess the risk for delirium in patients 70 years and older with the following questions: “Do you have memory problems?”; “During the past 24-hours, did you need assistance with your daily self-care?”; and “Were you confused during earlier hospital admissions or illnesses?”. When at least one of these questions is answered positively, there is an increased risk of delirium.

Exclusion criteria include a life threatening situation, being in a palliative phase at admission, an expected hospital stay of 24 hours or less, being legally incapable of participating, unable to communicate verbally, or a second hospital admission during the study period. If the patients are transferred to a participating unit, they are treated as a newly admitted patient; if the patients are transferred from a participating unit to a nonparticipating unit, they are excluded from the study.

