Inclusion criteria	70 years and over, at least one risk factor for delirium present	70 years and over at risk for delirium according to Dutch Safety Management Program
Exclusion criteria	intubation or respiratory isolation, aphasia, terminally ill, severe dementia, respiratory isolation, expected discharge within 48 hours after admission.	Same exclusion criteria except; exclusion when discharge is expected within 24 hours after admission. An added exclusion criterion; a second admission to a participating unit.
Protocols	Daily visitor program, feeding assistance program, early mobilization program, therapeutic activities program.	No adaptation
Volunteer shifts	Ranging from one to three times daily across protocols	Two times daily, one in the morning, one in the evening
HELP staff	Program director: oversees and supervises the entire program within a hospital.	Project leader :oversees all aspects the project within a hospital.
	Elder Life Specialist: responsible for day-to-day operations of the program, patient screening and coordination of the volunteers.	Volunteer coordinator: screens volunteers, makes sure volunteers attend the training, coordinates and provides support volunteers.
		Nurse Practitioners: screen patients, complete instruction forms for volunteers.
	Elder Life Nurse Specialist: clinical assessment and intervention skills, develops and implements practical strategies to prevent cognitive and functional decline, provides education to nursing staff, liaison with other health care specialties.	Nurse Practitioners: complete the measurements on delirium, quality of life, and cognitive function. They are in close contact with the nurses and instruct them when necessary.
	Geriatrician: provides geriatric assessment and consultation upon request, education to physicians, liaison with hospital medical staff	No adaptations
Staff nurses	ELS and ELNS are in contact with the staff nurses.	NP’s and volunteers are in contact with the staff nurses. The volunteers communicate with the staff nurses on patient level at the start and end of their shift.
Outcomes	Advised: brief cognitive screening test, such as SPMSQ, Activities of Daily Living scores, vital status, length of hospital stay, discharge destination, use of home services, hospital costs.	Incidence, duration and severity of delirium, 6-CIT, Activities of Daily Living Scores, diagnosis, length of stay, care consumption after discharge, health care costs, quality of life.

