### Delirium outcomes

The incidence of delirium will be diagnosed with the Confusion Assessment Method (CAM) [27], whereas the duration (number of days) and severity of the delirium will be assessed using the Delirium Rating Scale (DRS-R) [34]. In patients who fulfill the selection criteria, ward nurses will rate delirious symptoms daily using the Delirium Observation Scale (DOS) [35] at the end of each shift until discharge. This approach is already part of standard clinical practice and the VMS. When the patients receive a positive score for the DOS, the CAM will be administered by the nurse practitioner or geriatrician. In patients diagnosed with delirium according to the CAM, the Delirium Rating Scale (DRS-R) [34] will be administered daily by the nurse practitioner.

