### Statistical analysis

The aim of the main analysis is to compare the incidence, severity, and duration of delirium in pre- and post-HELP patient groups. To correct for the clustering of patients within wards and for baseline characteristics, multi-level analysis using the R statistical package will be used to evaluate differences in treatment outcomes between the two groups [40]. Estimates will be reported with 95% confidence intervals. The analysis will be conducted according to the intention-to-treat principle.

Missing data will be corrected using multiple imputation.

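### Excluding enrolled patients who are later transferred to a non-participating unit contradicts the stated intention-to-treat analysis

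*Protocol article*

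**What the plan says.** All references are to the protocol article.

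- **Transfer out** (Study population): "if the patients are transferred from a participating unit to a nonparticipating unit, they are excluded from the study".
- **Analysis principle** (Statistical analysis): "The analysis will be conducted according to the intention-to-treat principle".
- **Missing data** (same section): "Missing data will be corrected using multiple imputation".
- **Timing of enrolment** (Study population): "Eligible patients will be approached by the nurse on call for participation within 24-hours after hospital admission".
- **Observation for delirium** (Delirium outcomes): ward nurses complete the DOS "at the end of each shift until discharge". A positive DOS leads to a CAM, which defines the primary endpoint.
- **Transfer in** (Study population): "If the patients are transferred to a participating unit, they are treated as a newly admitted patient".
- **Repeat admission**: Study population excludes patients with a life-threatening situation and several other conditions, "or a second hospital admission during the study period". Table 1, under The intervention, words it differently: "An added exclusion criterion; a second admission to a participating unit".

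No section says that patients transferred out remain in the analysis set, are imputed, or are analysed under the unit and phase in which they enrolled.

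**The concern.** Enrolment comes within about a day of admission and the outcome window runs to discharge. A move to a non-participating unit is therefore generally a post-enrolment event. Removing patients on such an event is what intention-to-treat is meant to prevent.

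The rule makes no exception for a patient who already has a positive CAM, so an observed primary event can be deleted. Read literally, it also ends the three-month care-consumption calls for that patient and takes the patient out of the cost per prevented case.

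Removal does harm if it is related to delirium and differs between phases. Both are plausible. The Background says that delirium raises the risk of complications, and complications can lead to a transfer. HELP aims to maintain function and adds geriatric input, so transfers could differ between control and intervention periods. The documents establish neither link. The point of intention-to-treat is that the result should not depend on them.

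**Working it through.** **1. Do the statements conflict?** Enrolment is early, follow-up runs to discharge, and transfer can occur in between. One sentence takes the transferred patient out of the study; the other keeps all enrolled patients in the analysis. Multiple imputation does not bridge this, because it fills in values for patients who are in the analysis set, and these patients are not.

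**2. The plan's own figure, for context.** The Sample size section gives 470 per group for a 10-point difference (two-sided alpha 0.05, power 0.90) and fixes no control rate; it cites 10-40%. With the pooled-variance formula, 39% v 29% gives 470 and 40% v 30% gives 477. So 40% v 30% is close to what the plan appears to have used, and it serves as the base case. The conflict in step 1 does not depend on it.

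**3. Illustrative effect on the primary contrast.** The documents give no transfer rate, so these rates are assumptions. Let p be the true incidence, f the share of delirious patients transferred out, and 2% the share of non-delirious patients transferred out. Incidence among the patients who remain is

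p(1 − f) / [p(1 − f) + (1 − p)(0.98)]

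- p = 0.40, f = 0.10: 0.360 / (0.360 + 0.588) = 38.0%
- p = 0.40, f = 0.20: 0.320 / (0.320 + 0.588) = 35.2%
- p = 0.30, f = 0.10: 0.270 / (0.270 + 0.686) = 28.2%
- p = 0.30, f = 0.20: 0.240 / (0.240 + 0.686) = 25.9%

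| Delirious patients transferred, control / HELP | Control | HELP | Observed difference (true 10.0 points) |
|---|---|---|---|
| 10% / 10% | 38.0% | 28.2% | 9.7 |
| 20% / 20% | 35.2% | 25.9% | 9.3 |
| 20% / 10% | 35.2% | 28.2% | 7.0 |
| 10% / 20% | 38.0% | 25.9% | 12.1 |

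Differences are taken before rounding. With no true effect (40% in both phases), a 10% v 20% split gives 38.0% − 35.2%, a spurious difference of about 2.7 points in either direction.

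**4. Milder assumptions.** Take 3% of non-delirious patients transferred.

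- 10% of delirious patients in both phases: 38.22 − 28.45 = 9.8 points.
- 10% in control and 3% under HELP: 38.22 − 30.00 = 8.2 points.
- 3% in control and 10% under HELP: 0.4000 − 0.270/0.949 = 0.1155, or 11.5 points (0.11549 before rounding).

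**5. Events and power.** In the base case 470 × 0.40 + 470 × 0.30 = 188 + 141 = 329 cases are expected; losing 10-20% of them is 33-66 cases. In the plan's own two-group calculation at 40% v 30%, removing 2%, 5% or 10% of each group lowers power from 0.896 to 0.890, 0.881 or 0.863. The loss of power is small. The concern is removal that differs by phase.

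**The case against.** **No material bias is shown.** The documents give no rate, reason or destination for transfers. Geriatrics is a participating specialty, so some delirium-related moves may stay inside the study. Study procedure says that measurements are the same in both periods apart from the volunteers, which weakens the idea that the nurse practitioner's delirium measurement changes who is transferred, although The intervention does introduce that role as part of HELP. Equal removal hardly moves the difference. All of this stands. It limits what can be said about size and direction, but it does not remove the conflict between the two statements.

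**Exclusion might mean only that measurement stops.** On that reading the patient would stay in the analysis set and be imputed. Nothing in the article says so, and the rule stands in the paragraph of exclusion criteria. If that is what is meant, it needs to be written.

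**An article leaves analysis-set details to other documents.** That is true in general, but this article states both the exclusion and the principle, and the two disagree.

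**Stronger readings that the documents do not support.** A reader might infer from the transfer-in rule that a patient moving between two participating units is counted twice, once in each phase. The wording does not restrict where the patient comes from, and a move within the hospital is not a second hospital admission, so the text literally allows it. But the rule fits a first entry from a non-participating unit, and the Table 1 exclusion of a second admission to a participating unit points the other way. A reader might also infer that patients can enter after becoming delirious elsewhere in the hospital. If a transferred patient is treated as newly admitted, the natural reading applies the no-delirium criterion on arrival. Both are matters of wording, not demonstrated errors.

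**Conclusion.** The concern holds for transfers out. The rule in Study population contradicts the intention-to-treat statement in Statistical analysis, and no other section resolves it. It can delete observed primary events and can bias the primary contrast if transfer is related to delirium and differs by phase.

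The size and direction of any bias cannot be derived from the documents. Under the assumed rates, equal removal leaves 9.3-9.8 of a true 10 points, and unequal removal gives anything from 7.0 to 12.1. These figures rest on a 40% v 30% base case and on transfer rates chosen for illustration, so they show what is possible and do not estimate what will happen.

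For transfers in, there is an ambiguity between Study population and Table 1 about a patient already enrolled in another participating unit. It deserves a clarifying sentence because units in the same hospital start HELP three months apart, so one move can cross from control to intervention. It is not evidence of double counting.

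**What to change.** 1. Replace the transfer-out exclusion with a statement that every enrolled patient stays in the primary and cost analyses under the unit and phase of first enrolment.
2. Count any CAM-positive result obtained before transfer as a primary event.
3. Treat delirium status not observed after transfer as missing under the planned multiple imputation. Do not substitute DOS scores or chart entries from the receiving unit for the CAM. The DOS is a screening scale (reported specificities 0.77 and 0.88), the Discussion concedes that screening protocols are not always followed, and the preparatory attention to measurement covers participating units only. Mixing the two would change the outcome definition.
4. Continue the three-month care-consumption calls for transferred patients.
5. Report the number of transfers out by phase, with delirium status at transfer, so that a reader can judge whether removal would have mattered and how far the result leans on imputation.
6. Reconcile the newly-admitted rule with the Table 1 exclusion, so that each patient enters only once, and say that eligibility, including absence of delirium, is checked on arrival.

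The cost is a few sentences of wording, continued telephone follow-up for transferred patients, and a little more analysis work. The design and the intervention do not change. The change is best made before data are lost, because information not collected after an exclusion may be hard to recover.

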### Sample size

The sample size calculation was based on the primary endpoint incidence of delirium, as diagnosed by the Confusion Assessment Method (CAM) [27]. According to the literature, 10-40% of older hospitalized patients develop delirium [28-30]. HELP has been shown to reduce the absolute rate of delirium by 14.4%, which represented a relative risk reduction of 35.3% [17]. Thus, the difference in delirium incidence between the HELP-intervention group and the care-as-usual group was conservatively estimated to be at least 10%. To demonstrate this difference, using a two-sided test with an alpha of 0.05 and a power of 0.90, two groups of 470 patients are required, indicating a study population of 940 patients. Estimating that 15% of patients will not be willing to participate, the total number of patients to be included was estimated to be 1081 patients.

A total of 1648 patients ages 70 and older are hospitalized annually in the Diakonessenhuis. In the Hospital Gelderse Vallei, a total of 1393 patients aged 70 years and older are hospitalized annually. These hospitalizations result in 3,041 patients admitted per year, of whom at least two-thirds are expected to be at risk for delirium. This expectation is based on figures from hospitals that have already implemented the three question delirium risk assessment. This calculation should be sufficient for determining the total number of participants that are needed (n = 1,081) for the proposed study.

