Much attention will be paid to the recruitment, selection, training and coaching of volunteers. These individuals will receive a two day training and support from volunteer coordinators; a meeting will be organized every three months to allow the volunteers to share and evaluate their experiences. Before and after their activities, volunteers will also need to exchange information with nurses, which involves a change in the nurses’ work. The accessibility of the nurses will require attention from the project group.

A concern is the participation of an adequate number of older patients. The literature suggests that in older people, the refusal rate is higher than in younger populations. Several possible causes for this factor have been suggested. One reason described is that a lengthy and complicated patient letter with risks and benefits can be difficult to read and understand for frail older people [43]. The Medical Ethical Board considered this a low risk study; however, the Board has required that informed consent be obtained using a detailed and lengthy information letter, which may suggest that invasive research activities rather than additional care are being offered. It is therefore expected that fewer patients will be willing to sign consent.

HELP requires a fundamentally different view on the care organization and a change in the care process, including the introduction of methods of early recognition combined with care plans and the introduction of an Elderly Care Nurse Practitioner and trained volunteers to provide additional psychosocial support. Results of one cost-effectiveness study [17] showed that each patient who was prevented from becoming delirious saved the hospital $2,181. Although HELP has been implemented at a number of U.S., Canadian, Australian, and Taiwanese sites, only recently has the first implementation of a HELP-like program in a European hospital (Spain) been published [22]. The Dutch hospital care system and patient population are different than those of the USA. These differences have our utmost attention; in cooperation with the developers and users, we will try to implement HELP as closely as possible to the original protocols.

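### The 15% refusal allowance is multiplied on (940 × 1.15 = 1,081) instead of divided out (940 / 0.85 = 1,106), and the result is labelled as patients included, not patients approached

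*Protocol article*

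**What the plan says.** The Sample size section of the protocol article builds the number in three steps.

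- **Base size.** The section states: "two groups of 470 patients are required, indicating a study population of 940 patients". The test is two-sided at 0.05 with power 0.90, and the difference in delirium incidence "was conservatively estimated to be at least 10" percentage points.
- **Allowance.** The only adjustment after that is for refusal: "15% of patients will not be willing to participate, the total number of patients to be included was estimated to be 1081 patients".
- **Feasibility.** The next paragraph sets the expected admissions against "the total number of participants that are needed (n = 1,081").

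The Study population section separately describes nurses approaching eligible patients within a day of admission. The protocol therefore does distinguish being approached from taking part, but the Sample size section does not carry that distinction into its figures.

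**The concern.** Two things look wrong in the step from 940 to 1,081.

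The first is the formula. A refusal rate is a fraction of the people asked, so the number to ask is the number needed divided by the fraction who agree. Adding 15% of the number needed gives a smaller figure.

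The second is what 1,081 counts. People who decline are neither included nor participants, so a figure enlarged for refusal should count patients approached. The text uses it as a count of patients included and as the number of participants needed. A reader cannot tell whether the trial requires 940 or 1,081 consenting patients.

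What is at stake is a clear size requirement. The same printed figure means about 919 consenting patients on one reading and 1,081 on the other, so anyone comparing accrual with it, or reporting against it later, could reach opposite conclusions.

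**Working it through.** **Inputs from the Sample size section:** 470 per group and 940 in total; 15% unwilling to participate; stated result 1,081; 3,041 admissions a year aged 70 and older, of whom at least two-thirds are expected to be at risk.

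**1. Reproduce the stated figure.** 940 × (1 + 0.15) = 1,081.0. The match is exact, so 1,081 is not a rounding of some other formula.

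**2. Apply the refusal rate as described.** If 15% of those approached decline, 85% consent, and the number to approach is

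940 / (1 − 0.15) = 1,105.9, rounded up to 1,106.

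The difference is 1,106 − 1,081 = 25, or 25 / 1,081 = 2.3%.

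**3. Take the two readings of 1,081.**

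| 1,081 means | Consenting patients | Against 940 | What remains wrong |
|---|---|---|---|
| Approached | 1,081 × 0.85 = 918.9, about 919 | 21 short | The number (25 too low) and the label |
| Enrolled | 1,081 | 141 over | The derivation (a refusal allowance has no role in an enrolled count) and the conflict with 940 |

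**4. Power on the approached reading.** The plan gives no single control rate, only that "10-40% of older hospitalized patients develop delirium". It has to be assumed. I used the usual two-proportion formula with pooled variance under the null, equal groups and no continuity correction:

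n per group = [1.960 × √(2p̄(1 − p̄)) + 1.282 × √(p₁(1 − p₁) + p₂(1 − p₂))]² / (p₁ − p₂)²

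- For 39% v 29%: (1.313 + 0.854)² / 0.01 = 469.5, so 470 per group. This reproduces the plan's base figure.
- For 40% v 30%: 477 per group, close to it.

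Power with 470 per group, and with 918.85 / 2 = 459.4 per group:

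| Assumed rates | 470 per group | 459.4 per group | Loss (points) |
|---|---|---|---|
| 39% v 29% | 90.0% | 89.4% | 0.7 |
| 40% v 30% | 89.6% | 89.0% | 0.7 |
| 30% v 20% | 94.4% | 94.0% | 0.5 |
| 20% v 10% | 99.1% | 99.0% | 0.1 |

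Losses are taken from unrounded powers (for example 90.03 − 89.37 = 0.66).

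**5. Feasibility.** 3,041 × 2/3 = 2,027 at-risk patients a year. Over the 18 months given in the Design section that is 2,027.3 × 1.5 = 3,041, which equals the annual admissions only by coincidence. After 15% refusal it is 3,041 × 0.85 = 2,585. All of this is before the other exclusion criteria. Either 1,081 or 1,106 approached is well within it.

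**The case against.** The strongest reply is that nothing follows in practice. Taken at its word, 1,081 is a count of patients included, and enrolling that many would exceed 940. The Abstract says that all eligible at-risk patients on the participating units will be included, and the Design section fixes an 18-month calendar with units crossing over every three months. Accrual would then be set by admissions and time. The figure is used only to show that enough patients are available, and that conclusion is unaffected.

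Most of this stands. In particular, three stronger readings are not supported.

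- **That the trial will fall 21 patients short.** This holds only if 1,081 is the number approached, which the text never says.
- **That recruitment is steered by, or stops at, 1,081.** A reader might infer this from its description as the number needed, but no section sets it as a cap, a stopping point or a monitoring target.
- **That 15% is shown to be too low.** The Discussion does say "It is therefore expected that fewer patients will be willing to sign consent", which tempts one to recompute at higher refusal rates. It gives no rate and does not say that 15% will be exceeded. Whether 15% is realistic is a separate question from whether it was applied correctly.

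The reply does not rescue the text. If 1,081 counts enrolled patients, the reason given for raising 940 to 1,081 does not apply, since people who decline never enter that count. Nor can the 15% be taken as loss after enrolment, because the text ties it to willingness to participate. Condensing a protocol into an article does not explain it either: the inputs and the result are all printed, and they do not agree.

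**Conclusion.** The point holds as a minor error of arithmetic and labelling. On the plan's own inputs the number to approach is 1,106, not 1,081, and the printed figure is described as something that a refusal allowance cannot produce. One of these faults remains on either reading.

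The size is small: 25 patients (2.3%). On the approached reading only, there would be 21 fewer consenting patients than 940 and about 0.7 points less power. That power figure rests on an assumed control rate of 39–40%, chosen because it reproduces 470 per group or comes close, and on the plan's own comparison of two equal groups. At lower control rates within the cited range the loss is smaller still. This is not evidence that the trial is underpowered or that recruitment is at risk.

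**What to change.** In the Sample size section, replace the sentence on 1,081 with a statement that 940 consenting patients are required and that, at 15% refusal, 1,106 eligible patients must be approached (940 / 0.85). Use the same two terms in the feasibility sentence: compare the expected at-risk admissions with 1,106 approached, and keep 940 as the number of participants needed. If 1,081 enrolled patients was in fact intended, state that as the requirement and give a reason other than refusal for exceeding 940.

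The cost is one number and one label. Design, schedule and analysis do not change, and the expected flow of about 2,027 at-risk patients a year, before other exclusions, accommodates the corrected figure.
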